### Ethical Considerations

This study underwent ethical review and approval by the Datta Meghe Institute of Higher Education and Research institutional review board as per institutional guidelines (approval DMIHER[DU]IEC/2024/241). Informed consent will be obtained from all the participants involved in the study. The participants will be clearly informed about the study's purpose, procedures, potential risks, and benefits, specifically regarding the use of AI-assisted devices for tooth shade selection. Participant data will be anonymized to ensure privacy and confidentiality. Identifying information will not be included in any reports or publications. Strict data security measures, including encryption and secure storage, will be implemented to protect all participant information. Participants will be compensated for their time and involvement in the study with a modest stipend or gift card, the value of which will be specified in the informed consent form. Compensation will be fair and consistent for all participants. Details of the compensation will be clearly communicated prior to participation. No identifiable images of the participants will be included in the paper or supplementary materials. If such images are necessary, explicit consent will have been obtained from the individuals. Relevant consent forms and written communications will be uploaded during resubmission.

### Sample Size

The sample size (N) was calculated using the standard formula:

N = ((Z_α/2_ + Z_β_)^2^ × [P_1_(1 − P_1_) + P_2_(1 − P_2_)]) / (P_2_ − P_1_)^2^

Z_α/2_ = 1.96 for a 95% CI, representing the chosen level of statistical significance; Z_β_ = 0.84, which corresponds to 80% power; N represents the minimum number of samples required per group; and primary variable = reliability percentage.

Based on [12], the reliability of smartphone for classic shade determination = 7.7%, and the reliability of DSLR camera for classic shade determination = 15.4%.

Using a 5% level of significance and 80% power, the sample size calculation is as follows.

N = (1.96 + 0.84)^2^ × [0.077 (1 − 0.077) + 0.154 (1 − 0.154)] / (0.154 − 0.077)^2^

This yields a minimum required sample size of 221 participants per group.

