### Data Collection Procedure

A total of 221 participants will be recruited from the outpatient department. To choose their shade, study participants will be exposed to an intraoral scanner, a smartphone, and a DSLR. The study participants will be informed about the study and asked to sign a consent form prior to the procedure. The participants will be instructed to clean their teeth and take off any makeup before the test. The treatment will be performed on the patients' maxillary central incisors by using 3 different technologies: an intraoral scanner, a DSLR, and a smartphone camera.

Shade selection using a smartphone (iPhone 12; software version iOS 12.5.2.) will be performed using natural daylight or daylight-mimicking LED lights that are ideal for accurate color reproduction. The smartphone camera will be positioned parallel to the patient's face at a distance of 30 cm and zoomed in to focus on the teeth of interest, that is, the maxillary central incisors. Photos will be then imported into the Adobe Photoshop software to obtain the L*a*b values.

Photographic color selection will be done using the DSLR camera (Canon EOS 200D) with a macro lens for close-up shots with high detail and resolution. The DSLR camera will be set to manual mode to grant full control over exposure, aperture, and white balance settings, allowing for optimal customization to capture high-quality images for shade selection. The tooth would be placed at a distance of about 22-28 centimeters from the DSLR camera. The L*a*b values will then be acquired by importing the photographs into the Adobe Photoshop software.

For color selection, the Cerec Primescan (Dentsply Sirona) intraoral scanner will be used. The vita classic color selection mode will be activated in the scanner's software. We will scan the maxillary central incisor and note the color that is detected. The L*a*b values will be determined.

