### Expected Outcome

The primary outcome will be to evaluate if existing digital technologies, that is, DSLR camera and smartphone camera are equally efficient as the intraoral scanner for shade selection. The secondary outcome will be to establish a standardized protocol that ensures accuracy and efficiency of tooth shade selection by using readily available, economical digital devices.

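### The percentage that sizes the study is not tied to any step of data collection, to the stated outcome or to any listed analysis, so the stated 80% power applies to no planned test

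*Protocol article*

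**What the plan says.** All references are to the protocol article.

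- **Methods, Sample Size.** The study is sized on "primary variable = reliability percentage", with inputs "the reliability of smartphone for classic shade determination = 7.7" per cent and "the reliability of DSLR camera for classic shade determination = 15.4" per cent. The calculation is run "Using a 5% level of significance and 80% power" and closes with "This yields a minimum required sample size of 221 participants per group". Reliability is not defined; the rates are taken from a cited study.
- **Methods, Data Collection Procedure.** For the smartphone, "Photos will be then imported into the Adobe Photoshop software to obtain the L*a*b values". The DSLR workflow ends the same way. For the scanner, "The vita classic color selection mode will be activated in the scanner's software", the detected colour is noted, and L*a*b values are also determined.
- **Methods, Expected Outcome.** The primary outcome asks whether "DSLR camera and smartphone camera are equally efficient as the intraoral scanner for shade selection". No measure is attached.
- **Methods, Statistical Analysis.** The listed methods are means and SDs, Bland-Altman or intraclass correlation, paired t or Wilcoxon tests of mean shade differences between device pairs, subgroup analyses, and sensitivity and specificity with the scanner as reference and ΔE ≤ 2.0 as the match threshold.

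**The concern.** A sample size calculation gives power for one variable and one comparison. Here the variable is a proportion tied to classic shade determination, and the comparison is smartphone against DSLR. A tab-based reading of that wording is the natural one, but the article describes no step that gives a camera reading a tab. The outcome statement turns to a different comparison (each camera against the scanner) without a metric, and the analysis section does not mention the percentage.

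Two things are at stake. First, the 80% power is not a property of any analysis the study will run. Second, the primary result is left open: agreement on a shade tab, a ΔE match rate and a difference in mean L*a*b are different quantities, can point in different directions, and could each be presented as the answer once the data are seen. The clinical question, how often a camera leads to the same shade as the scanner, is a match rate, and a comparison of means alone would not answer it.

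**Working it through.** **1. Following the variable through the plan**

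| Section | What it would need to contain | What it contains |
|---|---|---|
| Sample Size | A defined binary result per participant and camera | A percentage for classic shade determination, undefined |
| Data Collection Procedure | A step giving that binary result | L*a*b values for all three devices; a VITA Classic shade for the scanner only; no repeat capture described |
| Expected Outcome | The same percentage | Equal efficiency with the scanner, no metric |
| Statistical Analysis | An estimate and comparison of the percentage | Continuous agreement, paired mean tests, sensitivity and specificity at ΔE ≤ 2.0; no comparison of proportions |

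The link is missing at each of the three steps after the sample size.

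**2. The plan's own figure**

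Inputs from Sample Size: P1 = 0.077, P2 = 0.154, z-values 1.96 and 0.84.

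- (1.96 + 0.84)² = 7.84
- 0.077 × 0.923 + 0.154 × 0.846 = 0.071071 + 0.130284 = 0.201355
- (0.154 − 0.077)² = 0.005929
- N = 7.84 × 0.201355 / 0.005929 = 266.25, so 267 per group

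The printed formula and inputs do not give 221. Under the same formula, 221 per group gives 0.077 / √(0.201355/221) − 1.96 = 0.59, which is power of about 72%. This is a separate matter from the present point, but the restated calculation should correct it.

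**3. What 221 would mean if the cited rates did apply**

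This assumes that 7.7% and 15.4% hold for the chosen match variable.

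- Smartphone: 221 × 0.077 = 17.0 matches; 95% half-width 1.96 × √(0.071071/221) = 3.5 percentage points.
- DSLR: 221 × 0.154 = 34.0 matches; 95% half-width 1.96 × √(0.130284/221) = 4.8 percentage points.

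Every participant is measured with all devices, so the comparison of cameras is paired. Let p11 be the proportion matched by both cameras. Then pd = 0.231 − 2·p11, d = 0.077, and

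n = (1.96·√pd + 0.8416·√(pd − d²))² / d²

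| Joint match rate p11 | Participants needed for 80% power |
|---|---|
| 0 (no joint matches) | 304 |
| 0.012 (independent: 0.077 × 0.154) | 273 |
| 0.04 | 198 |
| 0.077 (every smartphone match is also a DSLR match) | 100 |

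The article gives no p11, so whether 221 suffices cannot be settled even on its own rates. For a ΔE ≤ 2.0 match rate the article gives no expected rates at all.

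**The case against.** The best reply is that a match percentage is available. L*a*b values are obtained for all three devices, and Statistical Analysis supplies a binary rule, ΔE ≤ 2.0 against the scanner. A nearest-tab assignment could also be computed from the same values. It can be added that reliability is borrowed from a cited study whose definition is not shown, so exact tab agreement is only one reading, and that a journal article may leave a lookup rule to a fuller document.

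Much of this stands. A reader might infer that the variable cannot be derived at all, or that none of the 221 participants will yield a usable camera result. The documents do not support that: what is missing is the definition and the link, not the data.

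Two further inferences fail. A reader might take 7.7% and 15.4% as showing that the cameras fall far short of the scanner, but no scanner rate on that scale is given. A reader might also think the gap makes the Discussion's expectation of higher scanner reliability untestable. That expectation is out of reach because the scanner is itself the reference standard, whether or not tabs are assigned.

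The reply does not close the gap. The ΔE rule is given for sensitivity and specificity; it is called neither reliability nor primary, and nothing says the classic-shade rates carry over to it. Nor is this only condensed detail: the article itself names the primary variable, follows each device to its final output and lists the analyses, and these statements do not join up.

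**Conclusion.** The point holds as a break between the sizing variable and the rest of the plan. As written, the study would finish without its sizing percentage being produced by a stated step, named in the outcome or tested. The stated 80% power therefore attaches to no planned analysis.

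The size of the effect on power cannot be given as one number. If the cited rates are assumed to apply, the paired requirement runs from 100 to 304 against 221 planned. If a ΔE-based rate is intended, the article gives no basis for the sample size. The finding does not depend on what the cited study meant by reliability, only on the article's own sections not using the variable it declares primary. It should be settled before recruitment.

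**What to change.** Name one per-participant binary match as the primary variable and use it in Data Collection Procedure, Sample Size, Expected Outcome and Statistical Analysis. Either option would do:

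- **(a) Tab agreement.** Assign each camera's L*a*b values to the VITA Classic tab with the smallest ΔE, from one pre-specified table of tab values, and score agreement with the scanner's tab.
- **(b) ΔE match.** Score a match when the camera's values lie within ΔE ≤ 2.0 of the scanner's, as already used in Statistical Analysis, and state how the scanner's L*a*b values are obtained.

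Then report the proportion for each camera with a 95% CI, and compare the two cameras with a paired-proportion test such as McNemar's. Restate the sample size or the power at 221 for that measure and test, with the assumed joint match rate, and state as an assumption whether 7.7% and 15.4% apply. Keep the L*a*b comparisons as supporting analyses.

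The cost is protocol wording and a short calculation on values already planned, plus a tab table under (a). Neither option needs an extra visit or device. The downsides are that a match rate may look less favourable to the cameras than a comparison of means, and that the restated power may differ from 80% or call for a different number of participants.

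### The 80% power quoted for 221 belongs to smartphone versus DSLR in independent groups; for the primary paired comparison of each camera with the scanner, power is unknown

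*Protocol article*

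**What the plan says.** All places are in the Methods of the protocol article.

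- **Sample Size.** The sizing variable is a proportion: "primary variable = reliability percentage". The planning values are "the reliability of smartphone for classic shade determination = 7.7%, and the reliability of DSLR camera for classic shade determination = 15.4" percent. The formula uses the variance P1(1 − P1) + P2(1 − P2), which is that of two independent groups, and "N represents the minimum number of samples required per group". The error rates are two-sided 5% and 80% power: "Using a 5% level of significance and 80% power, the sample size calculation is as follows". The result is given as follows: "This yields a minimum required sample size of 221 participants per group".
- **Expected Outcome.** The primary outcome is whether "DSLR camera and smartphone camera are equally efficient as the intraoral scanner for shade selection".
- **Data Collection Procedure.** One set of 221 people is recruited, and the "study participants will be exposed to an intraoral scanner, a smartphone, and a DSLR", all on the maxillary central incisors.
- **Statistical Analysis.** Mean shade differences are tested by paired t or Wilcoxon signed-rank tests for all three device pairs. Agreement is described by Bland-Altman plots or intraclass correlation. Sensitivity and specificity of each camera are assessed against the scanner as reference, with ΔE ≤ 2.0 counting as a match. A multiplicity correction is intended.

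**The concern.** The only quantitative justification for 221 answers a different question from the primary one, in three respects.

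1. **Comparison.** It looks for a difference between the two cameras. The primary outcome is about similarity of each camera to a third device, for which no planning value is given. The Discussion says that the study supplying the planning values also examined intraoral scanning and found it more accurate, but no scanner figure is carried over.
2. **Design.** It assumes separate groups. The study has none, since each participant supplies a reading from every device. Paired power depends on how often the devices disagree on the same tooth, and the calculation does not state this.
3. **Endpoint.** It is sized on a proportion, while the planned test of smartphone against DSLR is on mean shade differences.

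At stake is what a reader may conclude from a non-significant camera-scanner difference. With 80% power printed beside 221, such a result could be taken as well-powered support for equal efficiency. The calculation supports no such inference.

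**Working it through.** **Inputs from Sample Size:** Z = 1.96 and 0.84, P1 = 0.077, P2 = 0.154, d = 0.154 − 0.077 = 0.077, d² = 0.005929, stated N = 221 per group.

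**Step 1. The plan's own figure.**
P1(1 − P1) + P2(1 − P2) = 0.071071 + 0.130284 = 0.201355.
N = (1.96 + 0.84)² × 0.201355 / 0.005929 = 7.84 × 0.201355 / 0.005929 = 266.25, so 267 per group. The stated 221 is not reproduced.
Power at 221 per group: 0.077 / √(0.201355/221) − 1.96 = 2.551 − 1.96 = 0.591, which gives about 72%. This slip is separate from the present point, but it must be kept apart in the steps below.

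**Step 2. The sized contrast in the actual paired design (McNemar).**
Let ψ be the proportion of participants in whom one camera is correct and the other is not.
N = (1.96√ψ + 0.84√(ψ − d²))² / d²
Power at n = Φ[(d√n − 1.96√ψ) / √(ψ − d²)]

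The document gives no ψ, so it is an assumption. It cannot be below 0.077, the case where every tooth the smartphone gets right is also right by DSLR. Under independence, ψ = 0.077 + 0.154 − 2 × 0.077 × 0.154 = 0.2073.

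| ψ | N for 80% power | Power at 221 |
|---|---|---|
| 0.077 | 100 | 98.8% |
| 0.15 | 196 | 84.5% |
| 0.17 | 222 | 79.7% |
| 0.2073 (independence) | 272 | 71.3% |

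Power of 80% at 221 therefore needs ψ of about 0.169 or less, a between-device correlation of about 0.2 or more. These figures use the full 5% level. With Bonferroni over three pairs, the plan's own independent-groups formula needs 356, and 221 gives about 56%.

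**Step 3. Pairing separated from the arithmetic slip.**
At independence McNemar needs 272, close to the 267 of the printed formula. With n = 267, paired power is Φ[(0.077√267 − 1.96√0.2073) / √0.201355] = Φ(0.815), about 79% at independence, and about 87% at ψ = 0.17. So of the fall from 80% to 71%, about 8 points come from using 221 instead of 267 and about 1 point from ignoring pairing. With positive correlation, the independent-groups formula is conservative.

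**Step 4. The primary question.**
No N or power can be derived from the document, because it gives no scanner value, margin, SD or discordance. The ΔE ≤ 2.0 criterion classifies a single reading; it is not a margin for a mean or a proportion. To show how far the answer depends on the missing inputs, take two one-sided tests on a paired mean difference, true difference 0, n = 221, and an assumed margin of m SDs of the paired difference. Power = 2Φ(m√221 − z) − 1.

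| Assumed margin | One-sided 5% | One-sided 2.5% |
|---|---|---|
| 0.15 SD | 44% | 21% |
| 0.20 SD | 82% | 69% |
| 0.25 SD | 96% | 92% |

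**Step 5. What 221 does give for camera-scanner agreement.**
Proportion with ΔE ≤ 2.0, 95% CI half-width at worst (50%): 1.96 × √(0.25/221) = 0.066.
Mean difference: 1.96/√221 = 0.132 SD of the difference.

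**The case against.** The best defence has four parts.

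- **Smartphone versus DSLR is a planned test.** True: it is one of the three device pairs in Statistical Analysis, so the calculation is not idle. But it is not the primary outcome, and it is to be tested on mean shade differences, not on the proportion used for sizing.
- **Pairing usually helps.** This also stands. Ignoring pairing is roughly neutral at zero correlation and conservative above it. A reader might infer from the 71% that the paired design leaves the study underpowered. The figures do not support that, because nearly all of this loss is the arithmetic slip.
- **The plan does contain a binary analysis.** A reader might infer that the sizing variable has no counterpart in the analysis. That goes too far: sensitivity and specificity against the scanner use the ΔE ≤ 2.0 match. What is not stated is that this match is the reliability percentage of the sample size, or that the cameras are compared on it. A named test could be left to a fuller plan.
- **The planning values.** It is tempting to read 7.7% and 15.4% as cameras being wrong in 85% to 92% of readings, and so as contradicting the expectation that they match the scanner. The article does not define reliability or its reference, and gives no scanner rate, so this does not follow.

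The article being condensed does not answer the main point. The sample size calculation is printed in full and is at odds with other sections of the same article.

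**Conclusion.** The point holds, and it should be corrected before recruitment. The stated 80% power is attached to a comparison (smartphone versus DSLR) and a design (independent groups) that are not those of the primary outcome. For each camera against the scanner, power at 221 is unknown; under the illustrative margins it lies anywhere from about 21% to over 90%. The documents do not show that 221 is too small for that question, nor that it is enough.

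For smartphone versus DSLR as a paired binary comparison, power at 221 lies between about 99% and 71% for discordance from 7.7% to 20.7%. This assumes that the planning values apply to the match variable, that device readings are not negatively correlated, and that no multiplicity correction is made.

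**What to change.** Recruitment had not begun at submission, so the basis can still be restated. No extra participants are needed.

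1. In Sample Size, delete the words per group and state 221 participants in total, each measured by all three devices.
2. Withdraw the 80% power claim for the primary question. State instead the precision of camera-scanner agreement at 221: a 95% CI half-width of at most 6.6 percentage points for the proportion with ΔE ≤ 2.0, and about 0.13 SD for a mean difference. Conclude equal efficiency only if that CI meets a margin fixed before data collection; otherwise report agreement with its CI.
3. For smartphone versus DSLR, give paired power at 221 as conditional on discordance (about 99% at 7.7%, 80% at about 17%, 71% at 20.7%), labelled as before multiplicity correction. Compare the binary match variable between the cameras by McNemar's test.
4. Acknowledge that the printed formula gives 267, so that 221 is no longer presented as its result.

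The cost is recalculation, wording and agreement on a margin. The downside is that the stated power becomes less favourable and that a claim of equal efficiency now has a criterion it can fail.

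### The printed sample-size formula gives 267, not 221, so the protocol's own calculation does not support the recruitment target at 80% power

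*Protocol article*

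**What the plan says.** The Sample Size section of the protocol article introduces its calculation with "The sample size (N) was calculated using the standard formula" and prints the usual expression for two independent proportions with unpooled variance, N being the number per group. It defines the first normal quantile as "1.96 for a 95% CI, representing the chosen level of statistical significance" and the second as "0.84, which corresponds to 80% power". The two proportions come from a cited study: "the reliability of smartphone for classic shade determination = 7.7"% and "the reliability of DSLR camera for classic shade determination = 15.4"%. The design targets are restated in the line "Using a 5% level of significance and 80% power, the sample size calculation is as follows". The four numbers are then substituted into the formula, and the section concludes: "This yields a minimum required sample size of 221 participants per group".

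The Data Collection Procedure section adopts that number as the size of the whole study: "A total of 221 participants will be recruited from the outpatient department". The Abstract gives the same figure. Each participant is measured with the smartphone, the DSLR camera and the intraoral scanner, and the Statistical Analysis section plans paired comparisons between devices.

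**The concern.** The formula, its inputs and its result all appear in one short section, so the result can be checked without outside information, and it does not follow from the inputs. This matters because 221 is the number to be recruited and this calculation is the only justification the article offers for it. If the formula needs more than 221, then recruiting 221 at the stated 80% power is unsupported by the protocol's own reasoning. According to the Results section, no participants had been recruited at submission, so the figure can still be corrected before it affects any data.

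**Working it through.** **Inputs, all from the Sample Size section.** Z for two-sided 5% = 1.96; Z for 80% power = 0.84; P1 (smartphone) = 0.077; P2 (DSLR) = 0.154.

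**1. The printed formula.** N = (Zα/2 + Zβ)² × [P1(1 − P1) + P2(1 − P2)] / (P2 − P1)².

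- (1.96 + 0.84)² = 2.8² = 7.84
- 0.077 × 0.923 = 0.071071; 0.154 × 0.846 = 0.130284; sum = 0.201355
- (0.154 − 0.077)² = 0.077² = 0.005929
- N = 7.84 × 0.201355 / 0.005929 = 266.25, rounded up to 267

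The stated 221 is not reproduced. The gap is 267 − 221 = 46, and 46 / 267 = 17%.

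**2. Could another convention give 221?**

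| Variant | N per group |
|---|---|
| Printed formula, unrounded normal quantiles | 267 |
| Pooled variance, two-sided | 270 |
| Pooled variance, two-sided, continuity correction | 295 |
| Arcsine, two-sided | 264 |
| Unpooled variance, one-sided 5% | 210 |
| Pooled variance, one-sided 5% | 213 |
| Pooled variance, one-sided 5%, continuity correction | 238 |

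None gives 221. A one-sided 5% test inflated for an assumed 5% dropout comes close (210 / 0.95 = 221.1), but it contradicts the printed 1.96, and the article states no dropout allowance.

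**3. What 221 gives under the printed formula.** Power = Φ((P2 − P1) / √(0.201355 / n) − 1.96). With n = 221, the standard error is √0.00091111 = 0.030185, and 0.077 / 0.030185 = 2.551. Power = Φ(2.551 − 1.96) = Φ(0.591) = 72.3%. With pooled variance it is 71.8%.

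Keeping P1 = 0.077 and 80% power, the formula returns about 221 when P2 is about 0.163: 7.84 × (0.071071 + 0.163 × 0.837) / 0.086² = 7.84 × 0.207502 / 0.007396 = 220.0.

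**4. The same contrast treated as paired.** Let ψ be the proportion of participants for whom exactly one of the two cameras is correct, and let d = 0.077. The McNemar approximations are:

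- n = (1.96√ψ + 0.84√(ψ − d²))² / d²
- power at 221 = Φ((d√221 − 1.96√ψ) / √(ψ − d²))

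The article does not give ψ. The two proportions confine it to the range from 0.154 − 0.077 = 0.077 to 0.154 + 0.077 = 0.231. If the two cameras' results were independent, ψ would be 0.154 × 0.923 + 0.077 × 0.846 = 0.207.

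| Discordance ψ | n for 80% power | Power at 221 |
|---|---|---|
| 0.077 (minimum) | 100 | 99% |
| 0.169 | about 221 | 80% |
| 0.207 (independence) | 272 | 71% |
| 0.231 (maximum) | 304 | 67% |

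**The case against.** The strongest reply is that the formula does not describe this design. All participants are measured with all devices, so the smartphone and DSLR results are paired and the independent-groups power does not apply. This stands. A reader might infer from the arithmetic that the study has 72% power, or a type II error of 28%, and so misses its 80% target. The article does not support that inference: with the same two proportions, power at 221 is above 80% if discordance is below about 0.169 and below 80% if it is higher. Pairing does not rescue the printed result, however. The article gives neither a paired formula nor a discordance, and 221 is presented as the output of an expression that returns 267.

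Two further readings are also unsupported. One is to apply a Bonferroni correction over the three device pairs to this proportion comparison and quote a still lower power. The Statistical Analysis section ties those pairs to paired t or Wilcoxon tests of mean shade differences, offers Bonferroni only as one example, and lists no test of the reliability percentages. The other is to predict that a null smartphone-versus-DSLR result would be over-read. The stated primary outcome compares the cameras with the scanner, so this is speculation.

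It can also be said that 221 per group and 221 in total are compatible when everyone is measured with every device. That is right, and the per-group wording is a point of clarity, not a second error.

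**Conclusion.** The arithmetic error is certain. The printed formula and inputs give 267, and the stated 221 is 46 (17%) too low. No standard variant consistent with the printed inputs gives 221, so the protocol's own calculation does not support the recruitment target at 80% power.

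The consequence for power is conditional. About 72% for 7.7% versus 15.4%, or 80% for about 7.7% versus 16.3%, holds under the independent-groups formula that the article prints. For the paired design that it describes, power for the same contrast lies between about 67% and 99%, depending on an unstated discordance. The 80% claim is therefore unsupported, but it has not been shown to be false for the study as it will be run. The correction is needed because the figure that sets recruitment is wrong as printed.

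**What to change.** Correct the result line in Sample Size to 267. If recruitment stays at 221, withdraw the unqualified 80% claim and do one of the following:

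- State that 221 gives about 72% power for 7.7% versus 15.4% under the printed formula, and add that this formula treats the devices as independent groups and so is not the power of the paired comparison.
- Replace the calculation with a paired (McNemar) one that states and justifies the assumed between-device discordance. About 0.169 or less would be needed for 221 to give 80%; showing power across 0.077 to 0.231 would make the dependence plain.

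In either case, say that 221 is the total number of participants, each measured with all three devices.

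If 221 is kept, this costs wording only, plus a less favourable or explicitly conditional power statement. Recruiting to 267 instead would add 46 participants.
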